### Implementation {16c}

To ensure efficient and accurate randomization, three syringes will be prepared per 24 h. The syringes will be labeled with patient numbers (patient 1, patient 2, or patient 3) based on their corresponding rank in the randomization list for that period. The solutions in the syringes will be identified by batch numbers, and the information of the patient to whom the syringe is dispensed will be recorded along with the date of injection. The syringes will be stored in a secure refrigerator in the delivery room for a maximum of 24 h. Unused syringes will be discarded after 24 h, and the randomization numbers for the unused syringes will be recycled for the following day’s preparations. This method ensures that the randomization process remains confidential and secure.

## Assignment of interventions: blinding

### Who will be blinded {17a}

Participants in the trial will be blinded to their treatment group. The investigator responsible for converting epidural analgesia to epidural anesthesia (referred to as “Investigator A”) will not be blinded, as they will be aware of the difference in volume between the two groups (20 mL versus 12 mL). However, the second investigator (“Investigator B”) who will take care of the patient in the operating room will be blinded, as will the patient’s obstetrician-gynecologist, who will assess the primary endpoint. Biostatisticians involved in the analysis of the data will not be blinded.

### Procedure for unblinding if needed {17b}

Unblinding will only be considered in the event of a serious adverse event that requires knowledge of the patient’s treatment assignment. Under no other circumstances will unblinding be allowed. If unblinding is deemed necessary, the randomization list will be consulted.

## Data collection and management

### Plans for assessment and collection of outcomes {18a}

The data are collected by the investigators at the time of the patient’s inclusion using a four-page sheet containing all the required information. See Additional file 1: “Data collection form.”

### Plans to promote participant retention and complete follow-up {18b}

Due to the short period of patient participation, which spans from the delivery room to PACU, we do not anticipate any patient loss during follow-up. Furthermore, as the only difference between the experimental and control groups is the solution injected during epidural conversion, no specific procedures or outcomes will be collected for patients who deviate from the protocol.

### Data management {19}

The software used for data management is REDCap. It is coupled with a dedicated MySQL database. The Information System Department (ISD) of the Bordeaux University Hospital provides hosting and maintenance of the database according to its procedures. The servers (Internet and database) are hosted in the ISD of the Bordeaux University Hospital (Talence, France). A backup is also hosted in Roubaix (France) and a second one is in a remote site located in Gravelines (France).

The management of the access rights to the software is under the responsibility of the REDCap administrator of the Bordeaux University Hospital. Data entry in the eCRF is under the responsibility of the investigator of the center. Any person other than the investigator who enters data into the eCRF must be trained and delegated by the investigator to do so. Only the data managers, the Clinical Epidemiology Unit team, and the auditors have direct access rights to the database. Prescribed treatments and clinical events are coded in the eCRF in order to perform data control and analysis. Data control are scheduled to verify the consistency and completeness of the data entered into the eCRF. The study data validation plan lists the data controls to be implemented. Requests for corrections are managed by the data manager. They are sent to the investigating center via the eCRF. The investigating team makes the necessary corrections to resolve the correction requests. After all correction requests are resolved, the data manager proceeds to the freezing of the database.

### Confidentiality {27}

In accordance with the law, the persons having direct access to the source data will take all the necessary precautions to ensure the confidentiality of the information relating to the research, to the persons involved, and in particular with regard to their identity and to the results obtained. These persons, as well as the investigators themselves, are subject to professional secrecy.

During the research or at its conclusion, the data collected on the persons who lend themselves to it and transmitted to the promoter by the investigators (or any other specialist) will be made anonymous. Under no circumstances should the names of the persons concerned or their addresses appear in clear text. Each participant will be given a confidential identification code, composed of a center number (2 digits), a patient number (2 digits), and a letter code (3 letters).

The sponsor will ensure that each person who participates in the research has given his or her consent for access to individual data concerning him or her and strictly necessary for the quality control of the research.

### Plans for collection, laboratory evaluation, and storage of biological specimens for genetic or molecular analysis in this trial/future use {33}

Not applicable: no biological specimen.

## Statistical methods

### Statistical methods for primary and secondary outcomes {20a}

The primary statistical analysis will compare the proportion of general anesthesia use between groups LEB and LE. The two groups will be compared using a chi-squared test, a corrected chi-squared test, or a Fisher’s exact test depending on the distribution of the theoretical numbers under the assumption of independence. The two-sided 95% confidence interval will be estimated for each group according to the exact binomial distribution.

Secondary outcomes will be compared according to the following principles. Quantitative variables will be compared by Student’s *t* test, Student’s test for unequal variances, or a non-parametric Wilcoxon test depending on the conditions of application of these tests. Linear regression models will be used to adjust for the major confounders. The assumptions of the model (normality and homoscedasticity of the residuals, linearity of the association for the quantitative factors) will be systematically verified. A transformation of the criteria may be envisaged in the event of deviation from the models’ hypotheses.

Qualitative variables will be compared by a chi-squared test, a corrected chi-squared test, or a Fisher’s exact test according to the distribution of the theoretical numbers under the hypothesis of independence. Logistic regression models will be used to adjust for the major confounders. The hypothesis of the models (log-linearity of the association for the quantitative factors) will be systematically tested.

A graphical representation will be associated as much as possible with the analyses

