## Methods: participants, interventions, and outcomes

### Study setting {9}

The patients will all be recruited from two academic hospitals, the University Hospital of Bordeaux and the Bayonne Hospital, southwestern France.

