### Sample size {14}

No previous study has investigated the use of general anesthesia after epidural extension with an alkalinized local anesthetic solution in extremely emergency caesarean sections during labor. However, a preliminary retrospective clinical audit conducted in 2019 at the Bordeaux University Hospital maternity ward found that the rate of recourse to general anesthesia was 100% (4 out of 4) in the lidocaine alone group, versus 0% (0/7) in the lidocaine-bicarbonate group. Although the sample size was small, the difference was significant (*p*=0.003). Therefore, caution should be exercised when using this preliminary result to calculate the number of subjects required for the current trial. Conservatively, assuming a general anesthesia conversion rate of 80% in the control group and 40% in the experimental group, 44 patients will be required in the lidocaine-bicarbonate group and 22 patients in the lidocaine group, for a total of 66 patients in a 2:1 ratio. The number of subjects required was calculated for a two-sided comparison test of two proportions with a 90% power and a 5% risk alpha.

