### Recruitment {15}

Each center will recruit as many patients meeting the eligibility criteria as needed, up to 66 patients.

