## Assignment of interventions: allocation

### Sequence generation {16a}

The randomization list will be established by the statistician of the Clinical Epidemiology Unit of the Bordeaux University Hospital before beginning the study. The 2 treatment groups will be unbalanced with a 2:1 ratio in favor of the experimental group (44 subjects in the LEB group and 22 subjects in the LE group). Randomization will be stratified by the investigating center. A document describing the randomization procedure will be kept confidential in the Clinical Epidemiology Unit.

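### The primary test pools two centres that randomisation stratifies by, and the only planned interval is one per arm, so the treatment effect gets no interval.

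*Protocol article*

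**What the plan says.** All references are to the protocol article.

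- **Design.** Study setting {9}: "The patients will all be recruited from two academic hospitals". Sequence generation {16a}: "Randomization will be stratified by the investigating center".
- **Primary test.** Statistical methods {20a}: "The two groups will be compared using a chi-squared test, a corrected chi-squared test" or Fisher's exact test, the choice depending on expected counts. None of the three uses centre.
- **Primary interval.** Same section: "The two-sided 95% confidence interval will be estimated for each group according to the exact binomial distribution".
- **Adjusted models.** Linear and logistic regression appear only under the principles for secondary outcomes. They are to adjust for major confounders, which are not listed. The section on additional analyses {20b} reads as not applicable.
- **Sample size {14}.** The calculation is "assuming a general anesthesia conversion rate of 80% in the control group and 40% in the experimental group", for a "two-sided comparison test of two proportions with a 90% power and a 5% risk alpha", "for a total of 66 patients in a 2:1 ratio".
- **Recruitment {15}.** No split between centres is fixed: "Each center will recruit as many patients meeting the eligibility criteria as needed, up to 66 patients".

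**The concern.** Stratified randomisation balances the arms within each centre, so centre-to-centre variation drops out of the true variance of the difference between arms. A pooled test still counts that variation in its standard error. If the centres have different general-anaesthesia rates, the standard error is too large, the test rejects too rarely under the null, and some power is lost.

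Separately, the primary objective is whether alkalinisation lowers the conversion rate. The reader will need to know by how much and with what uncertainty. Two per-arm intervals do not give that, and readers often misjudge them by looking for overlap. The article does not merely stay silent here: it chooses the interval to report, and that interval does not describe the treatment contrast.

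**Working it through.** **1. Reproduce the plan's sample size.** Inputs from Sample size {14}: 80% (LE), 40% (LEB), two-sided 5%, 90% power, 2:1.

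Pooled rate = (0.8 + 2 × 0.4)/3 = 0.5333.

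n(LE) = [1.960 × √(0.5333 × 0.4667 × 1.5) + 1.2816 × √(0.8 × 0.2 + 0.4 × 0.6/2)]² / 0.4² = (1.1976 + 0.6781)² / 0.16 = 21.99, so 22.

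This gives 22 LE + 44 LEB = 66, as stated. The plan is therefore sized for the pooled, uncorrected test (formula power 90.0%). At these rates the smallest expected count is 22 × 0.4667 = 10.3, so the uncorrected chi-squared test would be expected to apply.

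**2. Why pooling makes the test conservative.** Assumed: 33 patients per centre and exact 2:1 within centre (11 LE, 22 LEB). Under the null, the pooled test uses variance p(1−p) at the average rate p. The true variance uses the mean of p(1−p) over the two centres. The effective critical value is 1.960 × √(pooled/within).

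| Centre rates (null) | Within | Pooled | Effective critical value | Approximate level |
|---|---|---|---|---|
| 60% / 60% | 0.24 | 0.24 | 1.960 | 5.0% |
| 50% / 70% | 0.23 | 0.24 | 2.002 | 4.5% |
| 40% / 80% | 0.20 | 0.24 | 2.147 | 3.2% |
| 30% / 90% | 0.15 | 0.24 | 2.479 | 1.3% |

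**3. Exact check.** All outcomes were enumerated from the binomial distributions in the two centres. The stratified test is Cochran-Mantel-Haenszel (CMH) without continuity correction: [Σ(x − ma/n)]² / Σ[ab·m(n−m)/(n²(n−1))], summed over centres. Here x is LE events, m all events, a and b the arm sizes, and n = a + b.

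| Centre rates (null) | Pooled level | CMH level |
|---|---|---|
| 60% / 60% | 4.9% | 4.8% |
| 50% / 70% | 4.4% | 5.0% |
| 40% / 80% | 3.1% | 4.9% |
| 30% / 90% | 1.3% | 4.7% |

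With an assumed 48/18 split, the pooled level is 4.9%, 4.3%, 3.2% and 1.8%; CMH stays between 4.8% and 5.1%.

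**4. Power, average rates held at 80% and 40%.** Both arms are moved down in one centre and up in the other by half the gap.

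| Centre gap | Pooled (33/33) | CMH (33/33) | Pooled (48/18) | CMH (48/18) |
|---|---|---|---|---|
| 0 points | 89.1% | 89.3% | 89.1% | 89.2% |
| 20 points | 89.7% | 91.2% | 88.7% | 89.8% |
| 30 points | 90.5% | 93.3% | 89.2% | 91.4% |

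The gain from stratifying runs from 0.1 to 2.8 points.

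**5. What the per-arm intervals leave out.** Take an illustrative result near the planned rates: 18/22 (LE) and 18/44 (LEB).

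- Planned output, exact intervals: 59.7% to 94.8% and 26.3% to 56.8%.
- Risk difference: 81.8 − 40.9 = 40.9 points. The Wilson limits are 61.5% to 92.7% and 27.7% to 55.6%. Newcombe's method gives 40.9 − √(20.3² + 14.7²) to 40.9 + √(10.9² + 13.2²), about 15.8 to 58.0 points.
- Risk ratio: 0.50, 95% interval 0.33 to 0.75.

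A benefit of 16 points and one of 58 points are both compatible with these data. The per-arm intervals do not show this. With 16/22 and 20/44, the chi-squared p-value is 0.036 while the per-arm intervals (50% to 89% and 30% to 61%) overlap widely. That is no contradiction, but it invites misreading.

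**The case against.** **The test as written is valid.** It keeps the type I error at or below about 5% in every scenario above, and it matches the test that the sample size was built on. A significant result would stand. This is correct, so a reader who infers that the error rate is wrong in general would go too far: the departure exists only if the centres differ, and it is on the conservative side.

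**A large power loss is not shown.** A reader might simulate a centre shift of ±1.0 on the log-odds scale around 80% and 40% and find 75.7% power pooled against 83.6% with CMH, then blame pooling for the fall from 90%. That shift changes the average rates to 75.6% and 42.1%, a difference of 33.5 points instead of 40. At those rates with no centre difference, the pooled test already has only 74.1% power. The low figure comes from the smaller effect. The 8-point gain from CMH there needs centre gaps of about 32 and 45 points within arms. The article gives no centre-specific rates. That the LEB mixture has been used at Bordeaux since 2016 does not establish such a gap, since randomisation fixes the solution given.

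**The effect can be derived, and an analysis plan may add it.** The two proportions will be reported, so the point difference follows from them, and the article does not exclude a between-arm interval. Both are true. Still, the article states which interval will be given for the primary outcome, and it is not one for the contrast.

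**Centre in the secondary models.** One might go on to say that the secondary models omit centre. The article leaves the major confounders unlisted, so centre may be among them. That is silence and is not part of this point.

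**Conclusion.** The point holds as a modest, conditional improvement to the primary analysis.

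- **Pooling.** The analysis leaves out the factor that randomisation stratifies by. The cost is a test that becomes conservative as the centres diverge, and about 0 to 3 points of power at the planned average rates. If the centres are alike, the effect is negligible. The actual size is unknown, because the centre rates, the split between centres and the exact within-centre allocation are all assumptions here.
- **Effect estimate.** No between-arm measure with an interval is fixed for the primary outcome. This half does not depend on any centre difference and is the stronger one.

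Neither half threatens the validity of a significant result or the stated sample size.

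**What to change.** Before the data are analysed, amend the primary analysis in two respects:

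1. Make the primary test a centre-stratified Cochran-Mantel-Haenszel test, two-sided 5%, without continuity correction.
2. Name the centre-stratified (Mantel-Haenszel) risk difference with a two-sided 95% interval as the primary estimate, and keep the exact per-arm intervals as description.

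The cost is about two sentences and a little programming. No extra patients are needed: even with identical centres, the stratified test has 89.3% power against 89.1% for the pooled test at 22 and 44 patients.

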### Trial design {8}

This QETAL study is a bicentric patient-blinded, two parallel-arms randomized, controlled, clinical trial of superiority. Patients will be randomly assigned in a 2:1 ratio in group LEB (lidocaine-epinephrine-sodium bicarbonate) and group LE (lidocaine-epinephrine) respectively.

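### At 44 v 22 the continuity-corrected chi-squared test can only lose power against the Fisher test the plan already names; how much depends on cut-offs the article does not give (minor)

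*Protocol article*

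**What the plan says.** The section on statistical methods {20a} sets out three tests for the primary outcome: "The two groups will be compared using a chi-squared test, a corrected chi-squared test", or Fisher's exact test, "depending on the distribution of the theoretical numbers under the assumption of independence". The same three-way choice returns for binary secondary outcomes: "Qualitative variables will be compared by a chi-squared test, a corrected chi-squared test", or Fisher's test. Those outcomes include the maternal complications listed under Outcomes {12}. No expected-count cut-offs are given.

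The sample size section {14} fixes the layout: "44 patients will be required in the lidocaine-bicarbonate group and 22 patients in the lidocaine group, for a total of 66 patients in a 2:1" allocation, "assuming a general anesthesia conversion rate of 80% in the control group and 40% in the experimental group", for "a two-sided comparison test of two proportions with a 90% power and a 5% risk alpha". It does not say which of the three tests the 90% refers to.

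**The concern.** Fisher's test is valid at any expected count. A second small-sample test beside it is useful only if it sometimes rejects where Fisher does not, or if Fisher fails to hold the level. If neither is true, every table sent to the corrected test has the same or a smaller chance of a significant result, with no gain in return.

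The comparisons most exposed are those in which one cell is small: uncommon maternal complications, or a primary outcome far from its planning rates. A rule that changes test with the expected counts can also behave oddly at the boundary, so that a more extreme table gives a weaker conclusion than a milder one.

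**Working it through.** **Inputs.** From the sample size section: 22 LE, 44 LEB, planning rates 80% v 40%, two-sided 5%, 90% power. No dropout, as the article states ("we do not anticipate any patient loss during follow-up"). Cut-offs are assumed, in two versions:
- A: uncorrected if the smallest expected count is at least 5, corrected from 3 to below 5, Fisher below 3.
- B: uncorrected from 10, corrected from 5 to below 10, Fisher below 5.

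**1. Reproduce the sample size.** Pooled rate = (0.80 + 2 × 0.40)/3 = 0.5333. Without continuity correction,

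n(LE) = [1.960 × √(0.5333 × 0.4667 × 1.5) + 1.2816 × √(0.80 × 0.20 + 0.40 × 0.60/2)]² / 0.40² = (1.1976 + 0.6781)² / 0.16 = 21.99.

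This gives 22 + 44 = 66, as stated. With continuity correction, n = (21.99/4) × [1 + √(1 + 3/(21.99 × 0.40))]² = 25.6, so 26 + 52 = 78. The stated figure therefore belongs to the uncorrected test.

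**2. Compare the two small-sample tests.** There are 23 × 45 = 1035 possible tables. Each was given a corrected chi-squared p-value and a two-sided Fisher p-value (the sum of all table probabilities no larger than the observed one).
- Fisher rejects in 614 tables and the corrected test in 586.
- Rejected by the corrected test only: 0. Rejected by Fisher only: 614 − 586 = 28. Of these, 6 have a smallest expected count of 3 to below 5, and 12 have 5 to below 10.
- Maximum exact size over a common event rate: Fisher 3.7%, corrected 2.9%.
- The result is also one-way at 1% (0 v 24) and 10% (0 v 18), and at 5% for nearby arm sizes such as 22/43, 21/44 and 20/42.

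**3. Boundary behaviour under A.**
- 0/22 LE v 8/44 LEB: smallest expected count 22 × 8/66 = 2.67, so Fisher; p = 0.0445.
- 0/22 v 9/44: smallest expected count 22 × 9/66 = 3, so corrected. X² = (3 − 0.5)² × (1/3 + 1/19 + 1/6 + 1/38) = 6.25 × 0.579 = 3.62; p = 0.057. Fisher would give 0.024.

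One more event in the worse arm removes significance. The other rare-event losses under A are 1/22 v 11/44 (Fisher 0.049, corrected 0.091) and 1/22 v 12/44 (0.046, 0.063). The remaining three of the six are mirror images at very high rates: 22/22 v 35/44, 21/22 v 33/44 and 21/22 v 32/44.

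**4. Power, as exact binomial sums.** The rates other than 80% v 40% are illustrative; the article gives none for complications.

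| LE v LEB | Three-way rule, A | Three-way rule, B | B with Fisher replacing corrected | Uncorrected from 5, Fisher below |
|---|---|---|---|---|
| 80% v 40% | 89.1% | 87.4% | 88.7% | 89.1% |
| 5% v 25% | 40.3% | 51.2% | 52.3% | 53.9% |
| 0% v 20% | 53.0% | 67.7% | 67.7% | 67.7% |
| 10% v 30% | 39.2% | 37.2% | 41.5% | 45.2% |

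Under A, the chance of reaching the corrected branch at the planning rates is about 5 in a million. Under B it is 43%.

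**5. Size of the whole rule.** The maxima are 5.05% for A, 4.1% for B, 4.3% for B with Fisher in its middle band, and 5.07% for the two-test rule in the last column.

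**The case against.** The strongest reply is that the plan contains no error. It pre-specifies recognised tests, chosen from the table margins and not from the result, and cut-offs are ordinary content for an analysis plan that is not shown. That stands, and the absence of cut-offs is not the point made here. What the article does fix is a branch that Fisher dominates in this layout wherever the cut-offs lie.

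Four stronger readings are tempting, and the documents do not support them.
- *The trial loses power on its primary outcome.* Under A it does not at the planning rates (89.1% either way). A material loss needs LE near 95% to 100% together with LEB of about 70% or more, for example 77.7% v 89.2% at 100% v 75%. Under B that example shows no loss.
- *The rule discards harm signals against LEB.* This arises only under A, where all three lost rare-event tables do have LEB worse. Under B those tables go to Fisher. Even under A, tables with 8 or fewer events go to Fisher, and really rare harms are out of reach under any rule: at 2% v 10%, power is 3.2% with the corrected step and 4.5% without. Logistic regression is also planned for these outcomes.
- *The corrected test protects nothing.* That holds against the minimum-likelihood Fisher test. Against the uncorrected test it does lower the size: B has a maximum of 4.1%, against 5.07% for the replacement. With a doubled one-tail Fisher p-value the dominance also fails: 4 tables are rejected by the corrected test only and 2 by Fisher only.
- *The sample size contradicts the analysis.* It does not. The 22/44 figure reproduces with the uncorrected test, which the rule uses almost always at the planning rates under A. An exact 89.1% against a nominal 90% is routine.

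**Conclusion.** The point holds as a minor one. At 22 v 44 and two-sided 5%, the corrected branch gives up 28 rejection tables to Fisher and gains none, while Fisher already holds the level.

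The practical cost is conditional. With a 3-to-5 band it falls on uncommon secondary and safety outcomes (13.6 percentage points at 5% v 25%: 53.9 − 40.3) and leaves the planned primary comparison intact. With a 5-to-10 band it costs 1.3 points at the planning rates against Fisher in that band (88.7 − 87.4) and 1.7 against the uncorrected test (89.1 − 87.4), with no loss in the sparsest tables.

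The conclusion rests on the usual two-sided Fisher definition and on rejection at 5%. It does not say that every Fisher p-value is the smaller one: in 46 tables the corrected p-value is slightly smaller, without changing a decision at 5%. The cut-offs and the complication rates are assumptions.

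**What to change.** In the section on statistical methods {20a}, delete the corrected chi-squared test in both places, for the primary outcome and for the qualitative secondary outcomes. State instead that the uncorrected chi-squared test is used when every expected count is at least 5, and otherwise Fisher's exact test with the two-sided minimum-likelihood p-value. Naming that version matters, because the dominance does not carry over to the doubled one-tail p-value.

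Record that the maximum size of this rule is about 5.07%. If the team wants a strict 5% ceiling, Fisher throughout has a maximum size of 3.7% and 87.4% power at the planning rates.

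The sample size section {14} needs no correction. Optionally, it can name the uncorrected chi-squared as the test behind the 90%.

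The cost is a wording change, with no extra patients, data or staff. It should be recorded before outcomes are examined by arm, since the article says the biostatisticians are not blinded.
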